### Sample Size

Sample size calculations for the All Our Babies Cohort Study required complex considerations as maternal blood samples are destined for microarray analyses. Several power calculations for microarray methodologies exist, consequently sample size was determined and compared with two power calculation approaches. The first approach uses a two-class comparison model with a significance level of 0.001, a power of 0.95, one technical replicate per sample and estimated values of τ^2 ^+ 2 γ^2 ^= 0.25 and τ^2^/γ^2 ^= 4 (where τ^2 ^is the biological variance within class of log ratios and γ^2 ^is the technical variance of log ratios); the minimum sample size to identify a two-fold change in gene expression between classes is thus 25 patients in each study group [42,43]. An alternate approach is to consider the sample size required to detect a two-fold change in the expression levels of the 90% and 75% least-variable genes for a given set of false positive rates and power [42]; using previously published human tissue microarray data [43] and setting the false positive rates at 0.001 and a power of 0.9, this approach gave a minimum of 18 and 13 patients in each group to detect a two-fold change in expression levels for the 90% and 75% least-variable genes, respectively. Microarrays will be performed on RNA samples collected from 80 cases of spontaneous preterm birth and 80 matched controls (160 biological replicates) from samples collected at two time points (18-22 weeks and 28-32 weeks): a total of 320 microarrays. This sample size will allow prediction of:

1) idiopathic PTB (n~40), including

a) idiopathic PTB prior to 32 weeks gestation (n~13); and

b) idiopathic PTB between 32 and 37 weeks gestation (n~27);

2) PPROM and PTB (n~40), including

a) PPROM and PTB prior to 32 weeks gestation (n~13);

b) PPROM and PTB between 32 and 37 weeks gestation (n~27);

3) spontaneous PTB (n~80), including

a) spontaneous PTB prior to 32 weeks (n~25); and

b) spontaneous PTB between 32 and 37 weeks gestation (n~55).

Therefore, with a preterm birth rate of 9.1% in Alberta, an anticipated miscarriage rate of 5% and an anticipated loss to follow-up rate of 15% based on experience with other Alberta based cohorts [44], 2200 women will be enrolled in the All Our Babies Cohort Study. This should ensure 1800 women complete the study, of which approximately 180 will have preterm birth outcomes and approximately 120 of these will be spontaneous with or without PPROM.

The impact of access to routine prenatal care and health services on maternal variables at four months postpartum will be compared among the entire cohort. Although the sample size calculations for the All Our Babies Cohort Study were derived for the microarray analysis, the sample size of 1800 women is adequate to describe differences between groups with respect to health service utilization, maternal social support, psychosocial well-being, mental health, breastfeeding and parenting support using logistic regression [45-47].

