### Maternal Blood Specimens

Maternal blood samples are collected at 18-22 weeks gestation and at 28-32 weeks gestation either at a laboratory location or by a mobile phlebotomist. Participants are contacted at 17 and 27 weeks gestation by telephone and/or email to begin scheduling their first and second blood collections respectively. Collections can occur at any time of day and fasting is not required.

Four PAXgene™ blood RNA tubes (PreAnalytix/BD Canada, Mississauga, Ontario, Canada) are used at each blood collection. These tubes are specially designed to preserve RNA in whole blood at the time of collection. Blood is also collected into a heparin tube to isolate plasma (first collection), a serum collection tube (second collection) and into an EDTA tube for maternal DNA extraction.

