### Proposed Type and Frequency of Analysis

#### Transcriptomic Analysis

RNA will be extracted from samples collected from identified cases (spontaneous preterm births with or without PPROM) and controls (term deliveries). Cases and controls will be 'loosely matched' such that each group has a similar distribution of maternal ages, prepregnancy body mass indexes and smoking status. Extracted RNA will be aliquoted into three tubes - one for Agilent RNA quality assessment, one for the transcriptomic microarray, and one for validation of microarray findings by real time polymerase chain reaction. Samples will be run on Affymetrix microarrays in two batches of 40 cases and 40 controls. All statistical analyses will be conducted on the full dataset generated from the microarrays.

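### The 28-32 week prediction claim for births before 32 weeks is not supported as stated, because some of those cases cannot give a second sample

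*Protocol article*

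**What the plan says.** The Sample Size section of the protocol article plans microarrays on "80 cases of spontaneous preterm birth and 80 matched controls (160 biological replicates". Each woman is counted at both windows, and the array total is given as "from samples collected at two time points (18-22 weeks and 28-32 weeks): a total of 320 microarrays". The section then lists what this sample will allow the study to predict. The list includes "spontaneous PTB prior to 32 weeks (n~25" and "spontaneous PTB between 32 and 37 weeks gestation (n~55", and by subtype "idiopathic PTB prior to 32 weeks gestation (n~13" and "PPROM and PTB prior to 32 weeks gestation (n~13". No window is named for any stratum, and aim (a) under Objectives and outcome (a) under Proposed Outcome Measures compare cases with controls at both windows.

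The same section gives the minimum sizes: 25 per group by the first approach (power 0.95), and 18 or 13 per group by the second (power 0.9, for the 90% and 75% least-variable genes). It expects about 120 spontaneous preterm births, from which the 80 cases would come.

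On timing, Maternal Blood Specimens says "Maternal blood samples are collected at 18-22 weeks gestation and at 28-32 weeks gestation", with contact to schedule the second draw starting at 27 weeks. Under Transcriptomic Analysis, controls are loosely matched "such that each group has a similar distribution of maternal ages, prepregnancy body mass indexes and smoking status". Gestational age at the draw is not among the factors.

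**The concern.** Two statements in one section do not fit together. The array count gives every case a 28-32 week sample, yet nearly a third of the cases (25 of 80) are expected to deliver before that window closes. Questionnaire Data Collection provides for women who deliver before the second questionnaire, but no counterpart is stated for the second blood draw. Under Methods of Protecting Against Sources of Bias, sample loss is treated only as a matter of convenience and scheduling.

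The early strata have no slack. At n~25 and n~13 they sit exactly on two of the plan's minima, so any missing second sample takes them below. These births also matter clinically: the Background says that morbidity rises as gestational age falls and is highest before 28 weeks.

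The early cases who do have a second sample were drawn before their delivery, hence on average earlier in the window than term controls, who can be drawn anywhere in it. Within the early strata, a change in expression with gestational age could then pass for a difference between cases and controls.

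**Working it through.** **The plan's own figure.** (80 + 80) x 2 = 320. This reproduces exactly, and only if all 160 women have both samples. The strata add up within rounding: 25 + 55 = 80, and 13 + 13 = 26 against about 25.

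**Inputs.** From Sample Size: 80 cases, about 25 delivering before 32 weeks (about 13 per subtype), about 120 spontaneous cases available, minima 25, 18 and 13. Not in the document: f, the share of early cases without a second sample. It is ranged from 0 to 1. Cases delivering at 32-37 weeks are all taken to have a second sample.

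**Without replacement.** Second-window cases = 80 - 25f. Early cases = 25(1 - f). Per subtype = 13(1 - f).

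**With replacement from the 120.** If the 25/80 share holds (assumption), 120 x 25/80 = 37.5 deliver before 32 weeks. Cases with a second sample = 120 - 37.5f, of whom 37.5(1 - f) are early.

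| f | Of the 80: all | early | per subtype | Of the 120: all | early |
|---|---|---|---|---|---|
| 0 | 80 | 25 | 13 | 120 | 37.5 |
| 0.25 | 73.75 | 18.75 | 9.75 | 110.6 | 28.1 |
| 0.5 | 67.5 | 12.5 | 6.5 | 101.25 | 18.75 |
| 0.75 | 61.25 | 6.25 | 3.25 | 91.9 | 9.4 |
| 1 | 55 | 0 | 0 | 82.5 | 0 |

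Without replacement, arrays number 320 - 25f if only case arrays are lost (295 at f = 1), or 320 - 50f if an equal number of controls is dropped (270 at f = 1). With replacement, 80 second-window cases exist even at f = 1 (82.5), but then none of them is early. Keeping 25 early cases needs 37.5(1 - f) >= 25, so f <= 1/3. The subtypes give the same limit: 13 x 120/80 = 19.5, and 19.5(1 - f) >= 13 gives f <= 1/3.

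**How large might f be?** Suppose all early cases deliver at 28-32 weeks and draws are uniform over the window.
- Uniform deliveries: P(draw before delivery) = 1/2, so f = 1/2.
- Delivery density rising linearly over the window: P = 2/3, so f = 1/3, exactly the limit.

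Any delivery before 28 weeks raises f. Draws concentrated early in the window lower it.

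**Gestational age at draw.** With uniform draws and deliveries, the mean draw among sampled early cases is 28 + 4/3 = 29.33 weeks, against 30.0 in controls. Over the whole second-window case group (no replacement):
- f = 0.5: (55 x 30 + 12.5 x 29.33)/67.5 = 29.88 weeks
- f = 0.75: (55 x 30 + 6.25 x 29.33)/61.25 = 29.93 weeks

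The gap is about 0.7 week within the early strata, but only 0.07 to 0.12 week overall, which is less than a day.

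**The case against.** Several points on the other side stand.

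- **Overall power.** Even with every early case missing and none replaced, 55 cases remain, more than twice the minimum of 25. A reader might infer that the second-window comparison as a whole is underpowered or badly confounded. The figures do not support that.
- **The reserve.** A reader might infer that the 320 arrays cannot be filled. They can, from about 120 cases. What replacement cannot restore is the early stratum once f exceeds about 1/3, nor can it make those women anything other than undelivered at the draw.
- **The first window.** A reader might infer that early deliveries will be dropped from the 18-22 week analysis. No passage requires both samples for selection, so this follows only if cases are chosen for being complete at both windows.
- **Conditioning on an ongoing pregnancy.** Any screen at 28-32 weeks applies only to women still pregnant, so this is not a bias in itself. The claim should say so. A sample taken shortly before labour also contradicts nothing, since the woman is not in labour when it is drawn.
- **Assumptions.** The document gives neither the distribution of draws and deliveries nor the split at 28 weeks. The figures of 1/2, 1/3 and 29.3 weeks illustrate; they are not estimates from the plan.
- **Equal groups.** The minima are for equal groups, and the article does not say whether a stratum would be compared with its own controls or with all 80. With approach 1's variance of 0.25 (SD 0.5), a two-sided t test at 0.001 and a two-fold change of 1 on the log2 scale, 6.5 cases give power of about 0.30 against 6.5 controls and 0.93 against 80. On the natural-log scale the figures are 0.09 and 0.50. Falling below a minimum therefore need not end the analysis. But using all controls makes alignment on gestational age at draw more important.
- **Article format.** Details of adjustment may be left to a fuller document. The mismatch between the stated array total and the stated strata is in the article itself.

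**Conclusion.** The point holds for the strata delivering before 32 weeks at the second window, and not beyond them. The plan presents those strata as predictable at sizes equal to its own minima, while its array count assumes second samples that some of these women cannot give. Without replacement, any f above 0 takes the strata below 25 and 13. With replacement, about 25 early cases can be kept only if f is at most about 1/3, on the assumption that the 25/80 share holds among the 120.

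The difference in gestational age at draw is a concern within these strata (about 29.3 against 30.0 weeks under uniform assumptions) and negligible for the whole group (about 0.1 week). The number of missing samples cannot be fixed from the document; 25 of the 80 is the upper bound from early delivery.

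**What to change.** 1. In Sample Size, state the expected number of cases with a 28-32 week sample for each stratum, with the assumed share lacking one.
2. Drop the 28-32 week prediction claim for the strata before 32 weeks, or word it as conditional on being undelivered at the draw.
3. Select cases separately for each window, so that a woman without a second sample stays in the 18-22 week analysis.
4. At 28-32 weeks, match controls on gestational age at draw or adjust for it, above all in the early strata.

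The cost is a less favourable set of numbers for the early strata and a little more work in selection and analysis. Step 4 needs the date of each draw; the document does not say that it is recorded, so this is an assumption to confirm.

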### Proposed Outcome Measures

a) Transcriptomic profiles from maternal blood samples collected at 18-22 weeks and 28-32 weeks of pregnancy will be compared between two groups (women who deliver at term and women who deliver preterm) for patterns predictive of preterm birth.

b) Health service utilization, maternal social support, psychosocial well-being, mental health, breastfeeding and parenting support at four months postpartum will be compared between term and preterm deliveries.

c) The relative contribution of the environmental risk and the genetic risk will be compared between term and preterm deliveries.

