#### Statistical Analysis

Transcriptomic data, medical record data and self-report questionnaire data will first be analyzed univariately. Participant characteristics will be assessed and compared to the pregnant and parenting population in the province of Alberta and nationwide across Canada. Should transcriptomic signatures predictive of preterm delivery phenotypes be elucidated from the microarray analyses and validation, gene-environment interactions will be explored by integrating the transcriptomic data with the questionnaire and medical record datasets using appropriate statistical analytical techniques.

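### The sample size section claims prediction for nine overlapping preterm phenotypes at two sampling windows from calculations for a single two-class comparison, without saying which contrast decides

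*Protocol article*

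**What the plan says.** **Sizing.** The Sample Size section of the protocol article uses a "two-class comparison model with a significance level of 0.001, a power of 0.95" and concludes that "the minimum sample size to identify a two-fold change in gene expression between classes is thus 25 patients in each study group". A second approach covers the 90% and the 75% least-variable genes: "setting the false positive rates at 0.001 and a power of 0.9, this approach gave a minimum of 18 and 13 patients in each group", respectively.

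**Claim.** The same section plans arrays for 80 spontaneous preterm cases and 80 controls at 18-22 and 28-32 weeks (320 arrays). It then states "This sample size will allow prediction of" three phenotypes: idiopathic (about 40 cases), PPROM (about 40) and all spontaneous preterm birth (about 80). Each appears overall, before 32 weeks (about 13, 13 and 25) and at 32 to 37 weeks (about 27, 27 and 55). That makes nine entries on an equal footing.

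**Contrast.** Aim (a) under Objectives compares spontaneous preterm cases with term controls at both windows. Proposed Outcome Measures (a) says that profiles "will be compared between two groups (women who deliver at term and women who deliver preterm) for patterns predictive of preterm birth". Neither calls a contrast primary or ranks the windows.

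**Gate and validation.** Statistical Analysis says: "Should transcriptomic signatures predictive of preterm delivery phenotypes be elucidated from the microarray analyses and validation, gene-environment interactions will be explored". Transcriptomic Analysis describes validation as real-time PCR on another aliquot of the extracted RNA, and places all statistical analyses on the full array dataset.

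**The concern.** A calculation for one comparison is used to support a claim about nine phenotypes, two of which are smaller than two of the three minima just derived. Because the phenotypes are listed as equals and the later gate refers to phenotypes in the plural, a signature in any of them, at either window, can be read as success.

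Contrasts may also disagree. If a signature appeared only in idiopathic cases before 32 weeks, at one window, nothing stated says whether aim (a) has been answered. The PCR step would confirm that the expression difference in those women was measured correctly. It would not show that the difference exists beyond them. The section on the study's significance looks ahead to clinical screening of all pregnant women, so it matters which result may be called a predictive signature.

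**Working it through.** **1. The plan's own figure.** Inputs from Sample Size: two-fold change (1 on the log2 scale), variance 0.25, level 0.001 (taken as two-sided), power 0.95.

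- Per group: 2 x (3.291 + 1.645)^2 x 0.25 / 1^2 = 2 x 24.36 x 0.25 = 12.2, so 13. With the noncentral t it is 15.
- Both groups together: 4 x 24.36 x 0.25 = 24.4, so 25.

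The stated 25 per group is therefore reproduced only as a total. This is a separate matter, but it means that no power statement here should be anchored to 25 per group.

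**2. Number of contrasts.** 9 phenotypes x 2 windows = 18. This is an upper limit: women who deliver before or during 28-32 weeks may have no second sample.

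**3. Strata against the stated minima.**

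| Cases in stratum | 25 (two-class model) | 18 (90% least-variable) | 13 (75% least-variable) |
|---|---|---|---|
| about 13 (two strata) | below | below | meets |
| about 25 | meets | meets | meets |
| about 27 and above | meets | meets | meets |

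Using the variance of 0.25 directly, 13 per group has power 0.89 at 0.001 (noncentral t) for a two-fold change. The shortfall is thus against the minima that the section itself states; it does not mean that these strata have no power.

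**4. False positives over the family.** The article gives no signature-level error rate, so a two-sided 5% per contrast is an assumption.

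- If all 18 were independent: 1 - 0.95^18 = 0.603. They are not, because the phenotypes are nested.
- Null simulation, 200,000 runs, with disjoint cells of 13, 27, 13 and 27 cases combined into the nine listed groups, 80 controls and two windows:

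| Between-window correlation | All 80 controls shared | Size-matched controls |
|---|---|---|
| 0 | 0.39 | 0.43 |
| 0.5 | 0.37 | 0.41 |
| 0.8 | 0.32 | 0.35 |
| 0.95 | 0.27 | 0.30 |

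The range is 27-43%, or 0.27/0.05 = 5 to 0.43/0.05 = 9 times the nominal level.

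**5. Gene level.** The number of genes is not given. Assuming 10,000 to 50,000, the stated 0.001 gives 10 to 50 false genes in a single contrast with no signal, and 180 to 900 gene-by-contrast hits over 18. The single-contrast count comes from the number of genes, so naming a primary contrast does not remove it; control across genes is needed as well.

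**6. What the remedy does.** One phenotype at two windows, each at 5%: 1 - 0.95^2 = 9.75% if independent. At 2.5% each: 1 - 0.975^2 = 4.9%. For 80 v 80 with variance 0.25 the noncentrality is (1/0.5) x sqrt(80/2) = 12.6. Even Bonferroni over an assumed 50,000 genes at 2.5% has a critical value of only 5.03, so power for a two-fold change stays above 99.9%.

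**The case against.** **Silence.** A condensed article may leave the primary contrast, the multiplicity rule and the definition of a signature to an analysis plan. That is fair for missing detail, and no finding is made of it. What remains is a positive statement: the sample allows prediction of all nine phenotypes, although the calculation covers one comparison.

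**The overall contrast is there.** Aim (a) states it, Transcriptomic Analysis defines cases as spontaneous preterm births with or without PPROM, and 80 v 80 are selected. This stands. The gap is that it is not called primary, the windows are not ranked, the strata are not labelled, and Proposed Outcome Measures describes the case group simply as preterm.

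**Any hit opens the next stage.** A reader might infer this, but the text requires validation first. Validation on the same RNA gives little protection against chance, yet it is a stated condition. The interaction work is also already worded as exploration, and the section on significance expects positive findings to feed further validation.

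**A false signature is likely.** A reader might infer this from 18 tests. Only the independence figure of 60% exceeds one half, and nested groups are not independent. The 5% level is itself assumed, and a list of chance genes is not a validated signature.

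**Only the large groups can carry strict control.** On the plan's variance of 0.25 this is not supported. Under Bonferroni over an assumed 20,000 to 50,000 genes, 27 v 27 has power of about 0.95-0.97 for a two-fold change, and 13 cases against all 80 controls about 0.91-0.94.

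**Conclusion.** The concern holds in a limited form. The Sample Size section claims more than its calculation supports: nine phenotypes, up to 18 contrasts, none designated as deciding, and two strata below the section's own minima of 25 and 18. The route to a claimed signature is open to any phenotype, and the validation described cannot screen out chance differences between the women sampled.

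The inflation is about 27-43% against a nominal 5%. It rests on an assumed 5% per contrast, normally distributed contrasts, the listed group sizes, and between-window correlation from 0 to 0.95. This is substantial, but it does not make a false signature the expected result. The defect lies in what the study may conclude, not in how many women or arrays it needs.

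**What to change.** - **Proposed Outcome Measures and Sample Size:** name the contrast already in aim (a), all spontaneous preterm birth (80) versus term controls (80), as primary, and describe the case group in the same way in both places.
- **Windows:** treat 18-22 and 28-32 weeks as co-primary with the error split, for example 2.5% each. Do not make the later window conditional on the earlier one; that would block a signal present only at 28-32 weeks.
- **Genes:** within each window, control the false discovery rate across genes or use a permutation test of the whole signature.
- **Sub-phenotypes:** label the other eight exploratory, and say that they will be explored in this sample rather than that it will allow their prediction.
- **Statistical Analysis:** let only a primary result support the statement that a predictive signature was found. Say that interaction work based on a sub-phenotype signature rests on an exploratory result.

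**Cost:** wording only, with no further women, samples or arrays. Sub-phenotype findings lose confirmatory status, and each window is tested at 2.5% instead of 5%. With 80 per group, this has a negligible effect on power for a two-fold change.

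### The sample size is calculated for detecting a two-fold difference in single genes, but the protocol concludes that it allows prediction of every listed phenotype

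*Protocol article*

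**What the plan says.** All of the sizing is in the Sample Size section of the protocol article.

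- The first approach uses "a two-class comparison model with a significance level of 0.001, a power of 0.95, one technical replicate per sample", with a total variance of log ratios of 0.25. It concludes that "the minimum sample size to identify a two-fold change in gene expression between classes is thus 25 patients in each study group".
- The second approach takes the same error rate of 0.001 but a lower power, 0.9. Its result is reported thus: "this approach gave a minimum of 18 and 13 patients in each group to detect a two-fold change in expression levels". The larger number refers to the 90% of genes that vary least, the smaller to the 75%.
- The plan is then to run arrays at two time points on "80 cases of spontaneous preterm birth and 80 matched controls (160 biological replicates").
- The conclusion drawn is "This sample size will allow prediction of", followed by nine entries: idiopathic preterm birth (about 40; 13 before and 27 after 32 weeks), preterm birth with PPROM (the same numbers), and all spontaneous preterm birth (about 80; 25 before and 55 after 32 weeks).

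Proposed Outcome Measures describes a comparison of profiles between term and preterm deliveries "for patterns predictive of preterm birth". The Background faults existing markers for weak predictive value, sensitivity or specificity, and Significance of the Study looks ahead to screening all pregnant women.

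**The concern.** Detecting that a gene's mean expression differs between two groups is one question. How accurately a signature classifies an individual woman is another, described by sensitivity, specificity or discrimination. The calculations address only the first question, while the concluding sentence answers the second.

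Elsewhere the article uses prediction in its clinical sense, so the sentence will be read that way. A reader who sees 25 per group as the minimum and then strata of 27, 40, 55 and 80 will infer that each is large enough to establish prediction. Nothing in the section shows that for any of them.

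**Working it through.** **1. Reproducing the 25 per group.** Inputs from the Sample Size section: α = 0.001, power 0.95, variance σ² = 0.25 (SD 0.5), two-fold change. Sidedness and log base are not stated. For a comparison of two means with a normal approximation:

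n per group = 2σ²(z₁₋α/₂ + z_power)² / δ²

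Two-sided, (3.2905 + 1.6449)² = 24.358.

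- Natural log, δ = ln 2 = 0.693: n = 2 × 0.25 × 24.358 / 0.4805 = 25.35, close to the printed 25. The one-sided version gives 23.3.
- Log base 2, δ = 1: n = 2 × 0.25 × 24.358 / 1 = 12.2 per group, 24.4 in total.

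The printed figure is therefore the output of a single-gene mean-difference formula. As a per-group number it is recovered on the natural-log scale. The unstated base is a side matter and does not affect this point. The 18 and 13 of the second approach cannot be recomputed, because the gene variances come from a cited dataset.

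**2. What enters the formula.** Only α, power, variance and fold change. The second approach is described in the same terms. No sensitivity, specificity, area under the ROC curve, predictive value or interval width appears in either.

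**3. The listed groups against the section's own detection minimums.** Seven of the nine (about 80, 55, 40, 40, 27, 27 and 25) reach 25. The two of about 13 fall below both 25 and 18 and meet only the 13 given for the 75% least-variable genes.

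For 13 cases against 13 controls (two-sided t-test, log base 2, α = 0.001):

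- At the SD for which 25 per group gives 95% power (0.675), power is about 53%.
- At the SD for which 18 per group gives 90% power (0.603), power is about 68%.

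If all 80 controls are used against the 13 cases, these become about 94% and 98%. The detection shortfall therefore depends on which controls are used.

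**4. Illustration of precision for sensitivity.** Assumption, since the protocol gives no target: observed sensitivity near 80%, from a fixed rule with no model fitting, which favours the plan. Exact (Clopper-Pearson) 95% limits for x detected of n cases are the 0.025 quantile of Beta(x, n−x+1) and the 0.975 quantile of Beta(x+1, n−x).

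| Cases | Detected | 95% interval |
|---|---|---|
| 80 | 64 | 70–88% |
| 55 | 44 | 67–90% |
| 40 | 32 | 64–91% |
| 27 | 22 | 62–94% |
| 25 | 20 | 59–93% |
| 13 | 10 | 46–95% |

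Varying the assumption: near 70%, the interval is 59–80% at 80 cases (56/80) and 39–91% at 13 (9/13). Near 90%, it is 81–96% at 80 (72/80) and 64–99.8% at 13 (12/13). Selecting genes and fitting a signature on the same data would add uncertainty that these intervals leave out.

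**The case against.** **The comparison is what was planned.** The first objective and the first outcome measure are both framed as comparing transcriptomic patterns between cases and controls, and a two-class comparison is what the section sizes. This stands. A reader might infer that the calculation was made for the wrong analysis, but the documents do not support that. The fault lies in the conclusion drawn.

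**Prediction is conditional elsewhere.** Statistical Analysis and Significance of the Study both speak of predictive signatures only should they be found, and the latter mentions later validation. This reduces the risk of misleading a reader. It also leaves the unconditional sentence in Sample Size out of step with the rest of the article.

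**A two-fold change would be a strong marker.** With SD 0.5 on log base 2, a single such gene would have an area under the ROC curve of Φ(2/√2) ≈ 0.92. That is correct, but the calculation assumes such a gene rather than showing that one exists, and it is silent on the accuracy of a signature selected from a whole array.

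**Accuracy planning belongs in a fuller document.** A full evaluation plan can be left there, and its absence is not the complaint. The complaint is an affirmative statement that the printed calculation does not support.

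**Stronger readings to avoid.** A reader might infer that strata of this size cannot separate a useful predictor from the markers criticised in the Background. That section gives no accuracy values for those markers, so there is no benchmark. A reader might also set the printed 95% power against the chance that a lower confidence limit clears some threshold. Those are unrelated hypotheses, and the result depends on an arbitrary threshold. With true sensitivity 80%, the chance of the lower limit exceeding 60% is 73%, 54% and 42% at 40, 27 and 25 cases; for 50% it is 98%, 84% and 89%.

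**Conclusion.** The point holds as a mismatch between a calculation and the conclusion drawn from it. The section establishes a size for detecting two-fold differences in single genes; its statement about prediction has no support at any listed size. The n of about 80 is no exception: it has the narrowest illustrative interval, but no accuracy calculation was made for it either.

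The mismatch itself needs no assumption and follows from reading the inputs. The interval widths do rest on assumptions (observed sensitivity near 80%, no model fitting) and only indicate scale: about 19 percentage points wide at 80 cases and 49 at 13. They do not show that the study is too small, because the protocol sets no accuracy target to measure it against, and for the same reason no corrected sample size can be derived.

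**What to change.** In Sample Size, replace the prediction sentence with three statements:

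1. The sample allows detection of two-fold expression differences in the listed groups that reach the section's own minimum of 25 per group.
2. The two strata of about 13, if compared with equal numbers of controls, meet only the minimum for the 75% least-variable genes. A blanket detection claim over all nine entries would overstate these two.
3. Prediction is exploratory for all listed phenotypes, including all spontaneous preterm birth, in line with the conditional wording in Statistical Analysis and Significance of the Study.

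Add, as an illustration, the expected interval width for sensitivity at each stratum size, with the assumed sensitivity declared as an assumption.

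The cost is a few sentences and a short table. The stated claim becomes less favourable. No additional women or arrays are needed.
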